## Abstract

**Background:**

Asthma is one of the most prevalent chronic diseases of childhood and disproportionately affects children with lower socioeconomic status. Controller medications such as inhaled corticosteroids significantly reduce asthma exacerbations and improve symptoms. However, a large proportion of children still have poor asthma control, in part owing to suboptimal adherence. Financial barriers contribute to hindering adherence, as do behavioral factors related to low income. For example, unmet social needs for food, lodging, and childcare may create stress and worry in parents, negatively influencing medication adherence. These needs are also cognitively taxing and force families to focus on immediate needs, leading to scarcity and heightening future discounting; thus, there is the tendency to attribute greater value to the present than to the future in making decisions.

**Objective:**

In this project, we will investigate the relationship between unmet social needs, scarcity, and future discounting as well as their predictive power over time on medication adherence in children with asthma.

**Methods:**

This 12-month prospective observational cohort study will recruit 200 families of children aged 2 to 17 years at the Asthma Clinic of the Centre Hospitalier Universitaire Sainte-Justine, a tertiary care pediatric hospital in Montreal, Canada. The primary outcome will be adherence to controller medication, measured using the proportion of prescribed days covered during follow-up. Exploratory outcomes will include health care use. The main independent variables will be unmet social needs, scarcity, and future discounting, measured using validated instruments. These variables will be measured at recruitment as well as at 6- and 12-month follow-ups. Covariates will include sociodemographics, disease and treatment characteristics, and parental stress. Primary analysis will compare adherence to controller medication, measured using the proportion of prescribed days covered, between families with versus those without unmet social needs during the study period using multivariate linear regression.

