## Introduction

### Background

Asthma is one of the most prevalent chronic diseases of childhood, affecting 1 in 10 children and >3 million Canadians [1,2]. Asthma disproportionately affects children with lower socioeconomic status (SES) [3,4], who not only have a higher prevalence of asthma [5,6] but also have heavier symptom burdens, higher rates of emergency department (ED) visits [7-9], and more hospital admissions [2,4]. The higher burden of disease in these children has several overlapping causes including epigenetic changes related to stress during pregnancy [10], higher secondhand smoke exposure [9,11-13], and greater likelihood of living in environments where air quality is poor [8,14] and allergens are present [15]. Poorer housing quality is also associated with worse asthma control [13,16]. Moreover, families from lower SES have higher perceived barriers to care [17] and are more likely to have unmet care needs [18,19].

Controller medications such as inhaled corticosteroids significantly reduce asthma exacerbations while improving lung function and asthma symptom control [20-22]. Nonetheless, a large proportion of children have poor asthma control, in part owing to suboptimal adherence to inhaled corticosteroids, with objective adherence values ranging from 50% to 70% [23-26]. Previous reports [27-29] suggest that children with lower SES have lower adherence to controller medications, leading to worse asthma control and aggravating health inequities.

Adherence can be hindered by financial barriers that limit access to medication [8,19]. In addition, unmet social needs for food, lodging, and childcare may create stress and worry in parents, negatively influencing medication adherence [30]. Precarious employment, food insecurity, and unstable housing situations are also cognitively taxing and force families to focus on immediate needs [31,32].

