Scarcity refers to a state in which one’s cognitive resources such as attention and executive control are taxed by living with insufficient resources (money and time) [31]. Individuals may experience scarcity if they have high levels of stress at work, a relative who is acutely sick, or if they are in an unstable housing situation [32]. Although scarcity can affect anyone, those living in poverty may be particularly susceptible, given the financial constraints that require them to carefully balance immediate needs and upcoming expenses [31]. In pediatric asthma, the apparent unpredictable course of the disease is taxing for families. Psychological distress is frequently reported in qualitative studies of children with asthma and their parents [33], and caregiver life stress is associated with a heavier burden of asthma symptoms [34]. The relationship between stress and adherence in pediatric asthma has shown mixed results [35-37], suggesting that other variables such as scarcity may mediate the interaction.

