**Main independent variables**						
	*Unmet social needs*	A series of validated questions assessing employment [71], housing stability and ability to pay for utilities, [72-75], financial resource strain [76-78], food security [79], transportation [75], childcare [80], and parent education and health literacy [80,81]	Questionnaire	X	X	X
	*Scarcity, via executive control—*Eriksen flanker task	Speed of response and percentage accuracy [82-84], Δ accuracy between easy and hard condition	In-person computer-based task	X	X	X
	*Future discounting—*Kirby delay discounting task	27-item questionnaire assessing temporal discounting	Questionnaire	X	X	X

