**Exploratory measures**						
	*Capability*	Perceived Competence Scale [85,86]	Questionnaire	X	—	—
	*Motivation*	Treatment Self-Regulation Scale (adapted for adherence) [87]	Questionnaire	X	—	—
	*Perceived stress:* perceived stress scale	4-item measure used to understand how respondents perceive stress and how their feelings are impacted by certain situations [88]	Questionnaire	X	X	X
	*Asthma severity*: PPACI^d^	4-level PPACI assessed in the preceding 6-month period. On the basis of the number of doses per week of short-acting beta-agonists, use of oral corticosteroids within 14 days of a medical claim or hospitalization for asthma, any ED visit for asthma, and any hospitalization for asthma [89]	Medical chart	X	X	X
	*Access to resources*	Whether families accessed resources to which they were referred (social worker at local community health center)	Questionnaire	—	X	X
	*Asthma treatment satisfaction*	Single item inquiring who is primarily responsible for the child’s asthma management and 1 question drawn from the Asthma Medication questionnaire [90] adapted to inquire specifically about management of one’s child’s asthma	Questionnaire	X	X	X
	*Asthma responsibility questionnaire*	10-item measure examining the division of asthma management responsibilities between child and parent [91]	Questionnaire	X	—	X

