**Covariates**						
	Child’s *age* and *sex*	N/A^e^	Medical chart	X	—	—
	Child’s *gender*	N/A	Questionnaire	X		
	*Caregiver’s relationship with child*	Two items interrogating relationship to the child and whether respondent is the child’s legal guardian	Questionnaire	X	—	—
	*Caregiver’s gender*	N/A	Questionnaire	X	—	—
	*Caregiver’s marital status* and *living situation*	Single items assessing marital status and living situation as it relates to the child	Questionnaire	X	—	—
	*Postal code of the child’s residence*	N/A	Questionnaire	X	—	—
	*Caregiver’s level of education*	Elementary school or less, some high school, high school graduate, some college or technical school, college graduate, or completed a graduate degree	Questionnaire	X	—	—
	*Household income*	One item question based on the Canadian income survey [92]	Questionnaire	X	—	—
	*Presence of a smoker or e-cigarette user in the house*	2 question items investigating use of tobacco products or e-cigarettes in the last month [93]	Questionnaire	X	X	X
	*Responsibility for asthma management*	“Who is responsible for asthma management?”	Questionnaire	X	—	—
	*Child’s ethnicity, immigration status*, and *language spoken at home*	Questions using categories from Canadian census [94]	Questionnaire	X	—	—
	*Class of controller medication received during study period*	Inhaled corticosteroids and long-acting beta-agonists of leukotriene receptor antagonists	Medical chart	X	X	X

^a^The name of the variable in question has been italicized.

^b^Em dashes in the timeline signify that data for the associated variable will not be collected at the time point in question.

^c^X in the timeline indicate data collection for the associated variable at the time point (recruitment, 6-month follow-up, or 12-month follow-up) in question.

^d^PPACI: Pediatric Pharmacoepidemiology Asthma Control Index.

^e^N/A: not applicable.

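### The abstract lists parental stress as a covariate beside the primary unmet-needs regression, although the protocol describes stress as a possible step from needs to lower adherence

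*Protocol article*

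**What the plan says.** The abstract (Methods) states: "Covariates will include sociodemographics, disease and treatment characteristics, and parental stress". Its next sentence defines the primary analysis as a comparison of PPDC "between families with versus those without unmet social needs during the study period using multivariate linear regression".

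The abstract (Background) and the Introduction (Background) both say that "unmet social needs for food, lodging, and childcare may create stress and worry in parents, negatively influencing medication adherence". Later in the Introduction the evidence is qualified: "The relationship between stress and adherence in pediatric asthma has shown mixed results", and scarcity is offered as a possible mediator.

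The body of the article classifies stress differently from place to place:

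- Table 1 puts the Perceived Stress Scale ("4-item measure used to understand how respondents perceive stress and how their feelings are impacted by certain situations") under exploratory measures, not under covariates. It is collected at recruitment, 6 months and 12 months, as unmet needs are.
- The text describes it in the section Other Measures and Covariates.
- Statistical Analysis, aim 1, gives an open list of confounders that does not name stress. Aim 3 tests scarcity and future discounting as mediators, but not stress.

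Power Calculation and Feasibility claims 85% power for a 16-point PPDC difference between families with and without unmet needs, assuming that 50 of 200 have at least one need.

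**The concern.** On the protocol's own account, stress may lie between the exposure and the outcome. Adjusting for a variable in that position removes the part of the effect that runs through it. The regression would then answer whether needs matter at a fixed level of parental stress. That is a narrower question than whether families with unmet needs have lower adherence, and the power statement is about the latter.

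Nothing in the article argues that stress confounds the needs comparison, says that a direct effect is wanted, or plans a stress-free version of that comparison. The timing does not settle the matter either. Needs are taken over the study period and stress is measured at the same three visits, so stress is not established as coming before needs.

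At stake are the meaning of the primary coefficient and, if the path is material, the power to detect it.

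**Working it through.** **Inputs from Power Calculation and Feasibility.** SD of PPDC 33 points; difference 16 points; two-sided alpha 0.05; 50 families with and 150 without unmet needs; stated power 85%.

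**Step 1: reproduce the stated power.** The standard error is 33 × √(1/50 + 1/150) = 33 × 0.1633 = 5.39 points. Power is Φ(16/5.39 − 1.96) = Φ(1.01) = 84%. The t-test version also gives 84%. With 16.5 points (exactly half an SD) the result is 86%. The stated 85% is therefore confirmed. It comes from a two-group formula without covariates, so it refers to the total difference.

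**Step 2: what adjustment for stress leaves.** In a linear model, total effect = direct effect + effect through stress. If a share m of the total runs through stress, the adjusted coefficient is 16 × (1 − m). The documents give no value for m, so the values below are assumptions, and zero is among them. At an unchanged standard error, power is Φ(16(1 − m)/5.39 − 1.96). The last column also allows for an assumed correlation of 0.3 between stress and needs, which raises the standard error to 5.39/√(1 − 0.3²) = 5.65.

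| Assumed share through stress | Points left | Power, same standard error | Power, correlation 0.3 |
|---|---|---|---|
| 0% | 16.0 | 84% | 81% |
| 10% | 14.4 | 76% | 72% |
| 20% | 12.8 | 66% | 62% |
| 30% | 11.2 | 55% | 51% |

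Both columns ignore any fall in residual variance from adding stress to the model.

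**Step 3: what these shares imply.** With a the shift in stress due to needs (in SDs of stress) and b the loss of PPDC per SD of stress (in SDs of PPDC), the indirect effect is a × b × 33 points. A 10% share is 1.6 points, so a × b = 1.6/33 = 0.048. A 30% share is 4.8 points, so a × b = 4.8/33 = 0.145. The documents give neither a nor b.

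**Step 4: check by simulation.** One million families were simulated, 25% with needs, a total effect of 16 points and needs raising stress by 0.6 SD. Adding stress to the regression moved the size of the needs coefficient from 16.0 to 11.2 points with 30% mediated, and from 16.0 to 8.1 with 50% mediated. This agrees with 16 × (1 − m) to within simulation error.

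**The case against.** The strongest reply is that no sentence explicitly puts stress into the needs model. The covariate sentence follows a list of three main independent variables and may serve the analyses as a whole. Table 1 and the aim 1 confounder list point away from stress as a covariate, and the adjustment set for needs on PPDC may be left to an analysis plan that is not shown. This stands in part: the criticism must be conditional on stress entering that model. It does not remove the problem, because the abstract names the covariates directly before its only description of the primary regression, and the other sections disagree with it.

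Second, the path is worded as a possibility and the Introduction calls the evidence on stress and adherence mixed. This stands. The effect through stress could be nil, and then adjustment causes no such bias.

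Third, stress has other sources. The Introduction names stress at work as one cause of scarcity, which is a reason to keep stress as a covariate in the aim 1 models of scarcity and discounting. This also stands, and it favours a separate adjustment set for each question.

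A reader might go further and infer two more errors from Table 1. One is that controller class, recorded during the study, is adjusted for after exposure. The documents do not support this: Statistical Analysis does not say that 6- or 12-month class enters a model, and the schedule in Table 1 is a data-collection schedule. The other is that caregiver education is both a covariate and part of the exposure. Table 1 does list attained education as a covariate and a parent-education domain among the needs, but whether the two overlap depends on instruments that are not shown. Neither is put forward as an error.

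**Conclusion.** The point holds in conditional form. If parental stress is in the primary needs model, as the abstract's wording suggests, and if needs act partly through stress, as the protocol says they may, the coefficient is a direct effect and falls short of the total difference for which power is claimed. The inconsistent classification of stress across the abstract, Table 1, Other Measures and Covariates, and Statistical Analysis holds without any condition.

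The documents do not fix the size. The range in the working, from no loss to 4.8 of 16 points at a 30% share, rests on assumed shares. A reader might infer that the primary estimate is certainly biased toward no effect by a definite amount. The documents do not support that, because they give no path sizes and call the stress-adherence evidence mixed. The power arithmetic in the protocol is not in error.

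**What to change.** State that the primary regression of PPDC on unmet social needs estimates the total effect and does not adjust for parental stress. Report the stress-adjusted model only as a secondary analysis, labelled as a direct effect. Let stress remain a covariate in the aim 1 models of scarcity and future discounting if wanted, and name it there. Align the abstract, Table 1, Other Measures and Covariates, and Statistical Analysis so that stress has one stated role for each question.

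The cost is wording; no new data are needed. The downside is that stress arising from sources other than unmet needs is left as possible residual confounding in the primary estimate. The secondary model shows how far the coefficient moves when stress is added, but it cannot say how much of that movement is mediation and how much is confounding.

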**Results:**

The research activities of this study began in December 2021. Participant enrollment and data collection began in August 2022 and are expected to continue until September 2024.

**Conclusions:**

This project will allow the documentation of the impact of unmet social needs, scarcity, and future discounting on adherence in children with asthma using robust metrics of adherence and validated measures of scarcity and future discounting. If the relationship between unmet social needs, behavioral factors, and adherence is supported by our findings, this will suggest the potential for novel targets for integrated social care interventions to improve adherence to controller medication and reduce risk across the life course for vulnerable children with asthma.

**Trial Registration:**

ClinicalTrials.gov NCT05278000; https://clinicaltrials.gov/ct2/show/NCT05278000

**International Registered Report Identifier (IRRID):**

PRR1-10.2196/37318

## Introduction

### Background

Asthma is one of the most prevalent chronic diseases of childhood, affecting 1 in 10 children and >3 million Canadians [1,2]. Asthma disproportionately affects children with lower socioeconomic status (SES) [3,4], who not only have a higher prevalence of asthma [5,6] but also have heavier symptom burdens, higher rates of emergency department (ED) visits [7-9], and more hospital admissions [2,4]. The higher burden of disease in these children has several overlapping causes including epigenetic changes related to stress during pregnancy [10], higher secondhand smoke exposure [9,11-13], and greater likelihood of living in environments where air quality is poor [8,14] and allergens are present [15]. Poorer housing quality is also associated with worse asthma control [13,16]. Moreover, families from lower SES have higher perceived barriers to care [17] and are more likely to have unmet care needs [18,19].

Controller medications such as inhaled corticosteroids significantly reduce asthma exacerbations while improving lung function and asthma symptom control [20-22]. Nonetheless, a large proportion of children have poor asthma control, in part owing to suboptimal adherence to inhaled corticosteroids, with objective adherence values ranging from 50% to 70% [23-26]. Previous reports [27-29] suggest that children with lower SES have lower adherence to controller medications, leading to worse asthma control and aggravating health inequities.

Adherence can be hindered by financial barriers that limit access to medication [8,19]. In addition, unmet social needs for food, lodging, and childcare may create stress and worry in parents, negatively influencing medication adherence [30]. Precarious employment, food insecurity, and unstable housing situations are also cognitively taxing and force families to focus on immediate needs [31,32].

Scarcity refers to a state in which one’s cognitive resources such as attention and executive control are taxed by living with insufficient resources (money and time) [31]. Individuals may experience scarcity if they have high levels of stress at work, a relative who is acutely sick, or if they are in an unstable housing situation [32]. Although scarcity can affect anyone, those living in poverty may be particularly susceptible, given the financial constraints that require them to carefully balance immediate needs and upcoming expenses [31]. In pediatric asthma, the apparent unpredictable course of the disease is taxing for families. Psychological distress is frequently reported in qualitative studies of children with asthma and their parents [33], and caregiver life stress is associated with a heavier burden of asthma symptoms [34]. The relationship between stress and adherence in pediatric asthma has shown mixed results [35-37], suggesting that other variables such as scarcity may mediate the interaction.

In addition, poverty forces families to attend to immediate needs and makes it more challenging to think about, and invest in, the distant future. Future discounting represents the relative value one assigns to the future compared with the present [38,39]. Poverty is associated with higher levels of future discounting [40], which has been hypothesized to mediate the impact of lower SES on health outcomes [31,41,42]. Lower levels of future discounting (attributing a greater relative value to the future) are associated with several positive health behaviors, including influenza vaccination [43,44], physical activity [44,45], and abstinence from smoking [44,46-49]. In pediatrics, higher levels of future discounting correlate with lower medication adherence in type 1 diabetes [50,51]. In asthma, as in other pediatric chronic diseases, parents are asked to administer medications to their children daily to prevent future exacerbations and negative health outcomes. Levels of future discounting correlate with adherence to controller medication in young adults with asthma [52], but whether the same is true in children is unknown. Future discounting may be especially important to study in pediatrics, as medication adherence is a shared responsibility between parents and children [53-59] that evolves with the child’s age and developmental stage [53-60]. Children tend to be more present focused than parents [61], which may explain the decreasing levels of adherence to controller medication as the child or adolescent assumes greater responsibility for managing their asthma treatment [62].

In this project, we aim to investigate the relationship between unmet social needs, medication adherence, scarcity, and future discounting in pediatric asthma.

### Scientific Objectives

The overall aims of this project are to determine whether scarcity and future discounting are associated with medication adherence in children with asthma and to explore their role in the relationship between unmet social needs and adherence. Using a prospective observational study, we will investigate three primary relationships:

The relationship between scarcity, future discounting, and adherence to asthma controller medication;The association between unmet social needs, scarcity, and future discounting; andThe potentially mediating role of scarcity and future discounting on the relationship between unmet social needs and adherence to medication in children with asthma.

Our hypotheses related to each of these three primary relationships are the following:

We hypothesize that individuals experiencing scarcity and those with higher rates of future discounting will have lower adherence to asthma controller medication.We hypothesize that unmet social needs will be related to scarcity and future discounting in the following ways:Parents reporting unmet social needs will be more likely to experience scarcity and have greater levels of future discounting;The number of unmet social needs will correlate with level of scarcity and future discounting; andImprovements in a family’s unmet social needs during the study period will be associated with decreased scarcity and future discounting rates.We expect that scarcity and future discounting will play a mediating role in the relationship between unmet social needs and adherence to medication, with higher levels of both scarcity and future discounting specifically amplifying the impact of unmet social needs on medication adherence.

We will also examine two exploratory aims:

Examine whether adherence to medication mediates the association between unmet social needs and asthma outcomes: asthma control, ED visits, and hospitalizations.Document the progression of unmet social needs as the world moves to the next phase of the COVID-19 pandemic.

This project will help understand the relationship between cognitive factors, medication adherence, and unmet social needs, opening the door to developing targeted interventions to improve adherence to medication and, ultimately, children’s health outcomes.

